**PROTOCOL ( Alternative Second part)**

Leave "Multi-electrode lead" (postero)lateral vein position  
Add a second lead in the posterior or anterior vein

Start RA-pacing (100 bpm or otherwise highest tolerable rate)

(A) Pacing @ distal electrode. Make sure capture is obtained. If yes, run pacing protocol

(B) Pacing @ mid electrode. Make sure capture is obtained. If yes, run pacing protocol

(C) Pacing @ proximal electrode. Make sure capture is obtained. If yes, run pacing protocol

(D) Simultaneous pace @ all three electrodes  
Run pacing protocol

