## E Pacing protocol

## Pacing protocol

- Program optimal AV delay
- Turn pacing 'on' via connection box during 10-15 sec
- Turn pacing 'off' via connection box during 10-15 sec
- Repeat ON/OFF 3 times (so 4 times in total)
- Program other AV delays (+/- 20 ms & +/- 40 ms) and repeat pacing protocol

[figure not shown]

**Figure 4: Description of the pacing protocol.** In A the start of the protocol is depicted which involves imaging of the venous anatomy of the patient. The protocol can be separated into two parts, depending on the patient's anatomy. Part B is similar for every patient while part C or D is patient-dependent. In general, one part consists of BiV or Multivein using one or both of two opposite coronary veins (multivein approach). The other part consists of using up to three LV electrodes (BiV or QuadV) to pace from the (postero)lateral vein (multispot approach). Part E is displaying the pacing procedure for 1 out of total 5 AV delays during which the positive  $dP/dt_{max}$  will be measured. Each setting, as indicated by a horizontal line in the figure, will last 10-15 sec. The repetition of steps is used to increase sensitivity of the positive  $dP/dt_{max}$  measurements. Five AV delays will be assessed: optimal AV, optimal AV delay +/- 20 and +/- 40 ms.

At each pacing site, the evaluation of the effect of CRT will be performed approximately 4 times (repetition) in order to increase signal to noise ratio. Each setting lasts about 20 beats (10-15 sec) interspersed with baseline (AAI; also 20 beats, 10-15 sec) pacing. The heart rate will be elevated by atrial pacing to a base rate to 100 bpm or maximally tolerable rate (less than 10% drop in  $dP/dt_{max}$  from baseline no pace), to ensure a constant heart rate. The RV-LV (= VV-timing) intervals will be zero. Optimal AV-delay will be calculated using formulas ( $PAV_{ECG} = \min \{Ap-Pend + 30 \text{ ms}, Ap-RVs - 50 \text{ ms}\}$ ) derived

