## 8 Statistical Method and Data Analysis

### 8.1 Sample Size Justification

This study is powered for non-inferiority for the primary end point of difference in percentage change dP/dt max from baseline between Biventricular (BiV) pacing and Quadri-ventricular (Multispot) pacing. This is calculated as [percentage change in dP/dt max during Multispot] - [percentage change in dP/dt max during BiV]. Non-inferiority will be declared if the lower limit of a 1-sided 97.5% confidence interval of difference does not fall below -4%. Assuming the expected difference in percentage change dP/dt max between BiV pacing and multispot pacing is 0% and a standard deviation in differences of 8%, 34 patients would have 80% power to demonstrate non-inferiority for dP/dt max. The total sample size is increased to 40 patients to accommodate for non-compliance with protocol. Superiority testing will be performed if non-inferiority is met.

$$\begin{aligned}H_0: \Delta_{\text{multispace}} - \Delta_{\text{BiV}} &\leq -4\% \\H_1: \Delta_{\text{multispace}} - \Delta_{\text{BiV}} &> -4\%\end{aligned}$$

Previous literature suggests the average mean difference in percentage change between BiV and no pacing is 18%, in this study we consider Multispace non-inferior to BiV if the difference in their means is less than a quarter of the difference between BiV and no pacing [34]. No literature is available on the standard deviation of differences, which is the variability of the difference between pacing configurations within each subject. However we estimate that it would be less than half the variability seen when comparing differences across different patients.

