## 8.3 Analysis Methods

Descriptive statistics will be used to summarize the patient demographic and clinical characteristics at baseline. Data for qualitative variables will be presented as incidence rates (total number of patients, number of events, and percent). Data for continuous variables will be summarized using measures of central tendency and dispersion.

To calculate the mean LV dP/dt max difference and 95% confidence interval between pacing configurations a restricted maximum likelihood (REML)-based repeated measures approach (MMRM) will be used. Analyses will include the fixed, categorical effects of center (if sufficient number of patients per center available), pacing configuration, AV delay and if possible heartbeat. If the model is unable to support the beat-to-beat dP/dt values (i.e too much variability in the number of beats available per AV delay) then they will be averaged. The within-patient errors will be modelled using an unstructured (co) variance structure. If this analysis fails to converge, auto regressive, toeplitz, compound symmetric, and simple structures, with and without heterogeneous variances by pacing configuration will be tested. The (co)variance structure converging to the best fit, as determined by Akaike's information criterion, will be considered the primary analysis. Significance tests will be based on least-squares means and Type III sum-of-squares. Analyses will be implemented using SAS PROC MIXED.

Correlation coefficients will be calculated for each of the (non)-invasive measures with LV dP/dt, to account for the repeated measurements a linear mixed effects model will be used. Additional, a categorical variable of the best pacing configuration per patient will be calculated (the configuration that achieves the largest dP/dt value) and the agreement with each (non)-invasive

evaluation of best pacing configuration (also derived into a categorical variable) will be evaluated and tested with an unweighted Kappa statistic.

P-values will be evaluated based on a two-sided significance level of 0.05, and interaction effects will be evaluated at a significance level of 0.10. Except for the primary objective which is evaluated using a one-sided significance level of 0.025. No adjustments will be made for multiple testing. No imputation of missing data is planned.

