## 8.4 Analysis Populations

All patients who signed the informed consent document will be defined as the All Enrolled Population. The Study Population will be defined as all patients who provide informed consent and complete the study procedures or in who an attempt to start the study procedures is made. The Analysis Population is defined as patients who are enrolled and complete at least two of the three pacing configurations. Patients who are enrolled but are found to have an inclusion or exclusion criteria violation or a significant Clinical Investigational Plan deviation such that the clinical interpretability of the results obtained from the patient is impacted, will not be included in the primary analysis, but will be reported in the patient disposition table. Safety will be reported on the All Enrolled Population and the primary objective will be reported on the Analysis Population.

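### Section 8.3 names no population and no missing-configuration rule for the best-configuration kappa, so pooling patients with two and three configurations would bias it toward agreement

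*Combined protocol and SAP*

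**What the plan says.** Section 8.3 derives, for dP/dt, "a categorical variable of the best pacing configuration per patient will be calculated (the configuration that achieves the largest dP/dt value"). A matching label is derived for each invasive or non-invasive measure, and the two are compared and tested with an unweighted kappa at two-sided 0.05. Missing data are not imputed. This is the only method given for the Section 6.2.2 objective on identifying the configuration with the highest dP/dt max.

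Three other places bear on who can have a label.

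- Section 8.4 admits to the Analysis Population patients who "complete at least two of the three pacing configurations". It assigns only the primary objective to that population and names none for the kappa.
- Section 2 defines a single Multivein setting: RV with an anterior and a posterior LV lead.
- In Section 7.4.2, the Figure 4 legend says "Part B is similar for every patient while part C or D is patient-dependent". The alternative second part leaves the multi-electrode lead in the (postero)lateral vein and reads "Add a second lead in the posterior or anterior vein".

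**The concern.** The label is meaningful as a choice among three. A patient without Multivein can only be scored on two, by dP/dt and by the sensor alike, because the sensor is read during the same pacing runs. For an uninformative sensor, with available configurations equally preferred, chance agreement in such a patient is 1/2 rather than 1/3. Unweighted kappa uses one chance rate built from the pooled margins, which is lower than the true mixture of 1/2 and 1/3. The difference appears as agreement.

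The estimate and test for this objective would then be shifted upward by an amount that depends on venous anatomy rather than on the sensor. Sections 8.3 and 8.4 do not prevent this. Section 8.3 also lets method changes that leave the objectives intact be explained in the study report without an amendment, so the choice of who enters the kappa could be made after the labels are known.

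**Working it through.** **The plan's own figure.** The only sample size stated is for the primary comparison: "a standard deviation in differences of 8%, 34 patients would have 80% power to demonstrate non-inferiority for dP/dt max", with margin 4 and one-sided 0.025. The normal approximation gives (8 × (1.960 + 0.842) / 4)² = 31.4, so 32. With the noncentral t, power is 0.795 at n = 33 and 0.808 at n = 34, so 34 reproduces. Nothing is stated for the kappa. I use 34 as a working n; results at 40 are similar.

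**Inputs for the kappa.** From the documents: three configurations, one label each from dP/dt and the sensor, unweighted kappa, two-sided 0.05. Assumed:

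- a share f of patients lacks Multivein;
- both labels come from the available configurations;
- the sensor is independent of dP/dt.

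Multivein is taken as the missing one because Part B of Figure 4, which gives lateral BiV and Multispot, is common to all patients.

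**Formula.** With label probabilities p₃ₖ in complete patients and p₂ₖ in two-configuration patients, the same for both labels:

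- Po = f Σp₂ₖ² + (1 − f) Σp₃ₖ²
- Pe = Σ[f p₂ₖ + (1 − f) p₃ₖ]²
- kappa = (Po − Pe) / (1 − Pe)

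**Case 1: one value per configuration, equal preference** (nearest to the hypothesis of similarity in Section 3). At f = 0.15:

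- Po = 0.15 × 0.5 + 0.85/3 = 0.358
- Pe = 0.283² + 2 × 0.358² = 0.337
- kappa = (0.3583 − 0.3371) / (1 − 0.3371) = 0.032

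**Case 2: BiV is the largest of its five settings, all settings exchangeable.** Complete patients have probabilities 5/7, 1/7, 1/7 for BiV, Multispot and Multivein. With one vein unavailable, four BiV settings remain and the probabilities are 4/5 and 1/5. At f = 0.30:

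- Po = 0.3 × 0.68 + 0.7 × 27/49 = 0.590
- Pe = 0.74² + 0.16² + 0.10² = 0.583
- kappa = 0.016

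**Case 3: Multivein is best in half of complete patients for both labels**, the rest split evenly. At f = 0.30:

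- Po = 0.3 × 0.5 + 0.7 × 0.375 = 0.4125
- Pe = 0.35² + 2 × 0.325² = 0.334
- kappa = 0.118

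**Results.** Kappa is from the formula; rejection is by simulation of the kappa z-test with its null variance, n = 34. Simulated mean kappa agrees to within about 0.005.

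| f | Case 1: kappa; rejection | Case 2: kappa; rejection | Case 3: kappa; rejection |
|---|---|---|---|
| 15% | 0.032; about 7% | 0.009; about 5% | 0.073; about 10% |
| 30% | 0.054; about 9% | 0.016; about 6% | 0.118; about 18% |
| 50% | 0.067; about 11% | 0.020; about 6% | 0.143; about 24% |

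At f = 0 kappa is 0 in every case, and rejection was 4–6% in all the scenarios run.

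The excess lies in false agreement. In Case 1 at n = 40, rejections with positive kappa rise from 2.8% at f = 0 to 8.3% at f = 30% and 10.2% at f = 50%.

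**Check of the remedy.** Taking chance agreement within strata at f = 0.15 in Case 1 gives Pe = 0.15 × 0.5 + 0.85 × 1/3 = 0.358, equal to Po, so kappa is 0.

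**The case against.** The strongest reply is that the plan does not prescribe the faulty analysis. A reader might infer from Section 8.4 that every patient with two configurations receives a label. But the two-of-three population is tied to the primary objective only, and an analyst could restrict the kappa to complete patients without departing from the text. This stands: the defect is an unspecified population and rule, which permits best-of-two scoring but does not require it.

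Second, the alternative route may not lose Multivein. It still places leads in two veins and paces them together, and the Figure 4 legend calls the second part a multivein approach. If that pairing counts as Multivein, f falls. Section 2, however, defines the setting as anterior plus posterior, and nothing reconciles the two. The objection lowers the likely f but exposes a definition that the label depends on.

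Third, a reader might take the increase from 34 to 40 as a 15% missing rate (6/40). The plan gives another purpose: "The total sample size is increased to 40 patients to accommodate for non-compliance with protocol". It is not a rate of missing Multivein, so the 15% row above is only a point in an assumed range.

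Fourth, Section 8.3 does not limit BiV to its reference setting. If BiV is scored as the best of five, the bias nearly vanishes (Case 2). This also stands. In the other direction, Section 3 cites work in which an added LV lead raised dP/dt max and calls it comparable to the two-vein approach here. A preference for Multivein is therefore plausible, though not quantified.

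**Conclusion.** The point holds as a gap with a known direction of bias and a conditional size. If two-configuration patients are pooled on their available configurations, kappa for an uninformative sensor is pushed above zero. Over the assumed range f = 15–50%, the shift is about 0.03–0.07 and rejection 7–11% under equal preference. Rejection is close to nominal if BiV is the best of five settings, and 10–24% if both labels favour Multivein in half of complete patients.

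These figures rest on an undocumented f, on undocumented preferences, and on both labels being limited to the same available configurations.

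It would go too far to say that the plan will show agreement for a useless sensor. Under equal preference the false kappa is small, and the test still fails to reject in about 89–93% of trials. The issue concerns one secondary objective of an exploratory study. The kappa plays no part in the primary non-inferiority comparison, whose conclusion is unaffected.

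**What to change.** Add to Section 8.3 that the best-configuration labels and kappa are computed only in patients with BiV, Multispot and Multivein all measured, and that this number is reported. If two-configuration patients are to be kept, take chance agreement within strata of available configurations (a stratified kappa), or test by permuting sensor labels within those strata. Reconcile Section 2 with the alternative second part of Figure 4, stating whether that two-vein setting counts as Multivein for this analysis.

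The cost is a sentence or two, written before any labels are derived. The complete-case version loses patients: of 40, it keeps 34, 28 or 20 at f = 15, 30 or 50% (40 × (1 − f)). The stratified version keeps all of them.

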#### 6.2.2 Secondary Objectives

The secondary objectives of this study are to:

- Compare the positive LV dP/dt max from the multi-vein LV pacing configuration to the standard single spot LV pacing.
- Compare the positive LV dP/dt max from the multi-vein LV pacing configuration to the multispot LV pacing.

- Correlate the (non)invasive measures (blood pressure, electrocardiographic mapping and RV/LV EGM timings) obtained during the three pacing configuration's to the positive LV dP/dt max measures obtained.
- Evaluate the non-invasive measures ability to identify the pacing configuration with the highest positive LV dP/dt max.
- Evaluate the within patient variability in positive LV dP/dt max measures.

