## 6.4 Minimization of bias

Potential sources of bias in this study may result from selection of subjects, treatment of subjects, and evaluation of study data. Methods incorporated in the study design to minimize potential bias include but are not limited to:

- Subjects will be their own control, and study measurements have been designed to minimize the impact of within-subject temporal variation.
- Subjects will be screened to confirm eligibility for enrollment with defined inclusion/exclusion criteria prior to enrollment (See Section 6.3 Subject Selection)
- Subject demographics will be collected at the enrollment visit on possible differences that may affect primary endpoints.
- Data collection requirements and study procedures will be standardized across all study centers, including identical and calibrated equipment.
- All implanters in the study will be experienced in the placement of LV leads, performing EP procedures, performing LV pressure measurements.
- All study center personnel and Medtronic personnel will be trained on their respective aspects of the study using standardized training materials. All study clinicians will be trained on and required to follow the Clinical Investigational Plan.

In summary, potential sources of bias that may be encountered in this clinical investigation have been considered and minimized by careful study design.

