**PROTOCOL (Second part)**

RePlace "Multi-electrode lead" in anterior vein position  
Add a second lead in the posterior vein

Start RA-pacing (100 bpm or otherwise highest tolerable rate)

(A) Pacing @ distal electrode. Make sure capture is obtained. If yes, run pacing protocol

(B) Pacing @ mid electrode. Make sure capture is obtained. If yes, run pacing protocol

(C) Pacing @ proximal electrode. Make sure capture is obtained. If yes, run pacing protocol

(D) Simultaneous pace @ all three electrodes  
Run pacing protocol

D

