## 8.2 Study Endpoint

During the study all hemodynamic and electrophysiological data is continuously collected. The primary endpoint for this study is the positive dP/dt max value during BiV pacing and Multispace pacing. These data will be calculated offline using pre-determined filter-settings and algorithms. The values will be obtained on a beat-to-beat basis. To reduce variance, in particular the positive dP/dtmax values, each pacing setting is repeated 4 times. A similar approach will be taken for the (non)-invasive secondary endpoints.

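### Section 8.3 picks each patient's best configuration by the dP/dt value without its AAI baseline, so drift between the two procedure parts can alter the reference label for the kappa analysis

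*Combined protocol and SAP*

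**What the plan says.** - **Label.** Section 8.3 derives one categorical variable per patient, "the configuration that achieves the largest dP/dt value", and compares it by unweighted kappa with the best configuration according to each (non)invasive measure. It names no baseline, procedure part or time.
- **Objective served.** Section 6.2.2: "Evaluate the non-invasive measures ability to identify the pacing configuration with the highest positive LV dP/dt max".
- **Scale elsewhere.** Section 8.1 powers the study on the "difference in percentage change dP/dt max from baseline between Biventricular (BiV) pacing and Quadri-ventricular (Multispot) pacing". Section 8.2 drops the baseline: "The primary endpoint for this study is the positive dP/dt max value during BiV pacing and Multispace pacing".
- **Baseline.** Section 7.4.2 (pacing protocol): "Each setting lasts about 20 beats (10-15 sec) interspersed with baseline (AAI; also 20 beats, 10-15 sec) pacing". The cycle is repeated: "Repeat ON/OFF 3 times (so 4 times in total").
- **Order.** In Figure 4, the first part covers the distal, mid and proximal electrodes in the (postero)lateral vein and then all three together. The second part moves the multi-electrode catheter to the anterior vein, with the instruction "Add a second lead in the posterior vein". In an alternative second part the catheter stays where it is and a second lead is added.
- **Stated protection.** Section 6.4 says that "study measurements have been designed to minimize the impact of within-subject temporal variation".

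**The concern.** Configuration and procedure part are confounded. If underlying contractility rises or falls between the parts, the whole of that change enters the Multivein value and none of it enters lateral BiV or Multispot. The four repetitions do not help, because all repetitions of a setting fall within one part. The adjacent AAI runs would largely cancel such a change, and they are already recorded, but the rule in 8.3 does not use them.

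The label is the reference standard against which the sensors are judged. If drift helps to set it, kappa partly measures agreement with procedure time rather than with pacing effect. The direction is not fixed. A sensor that does not drift with dP/dt will agree less often. A pressure signal that drifts with dP/dt can move both labels together and raise kappa.

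**Working it through.** **1. Time between the parts.** Section 7.4.2 gives five AV delays, four ON/OFF cycles per delay, and 10-15 s each for ON and OFF (20-30 s per cycle).

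5 x 4 x 20-30 s = 400-600 s = 6.7-10 min per setting.

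Four first-part settings take 4 x 6.7-10 = about 27-40 min before the second-part lead work begins. The plan puts the whole procedure at 60 to 120 min.

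**2. Inputs from section 8.1.** These are an 18% mean gain for BiV over no pacing, an SD of within-patient differences of 8 points, and a margin of 4 points. The plan's sample size follows from the last two. A paired t-test with one-sided alpha 0.025 and n = 34 has 80.8% power (33 patients give 79.5%), so 34 reproduces. That figure does not depend on this point.

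**3. How much drift matters.** At an 18% gain, a proportional baseline shift d moves the dP/dt value by 1.18 x d, in points of the original baseline. A shift of 4/1.18 = 3.4% equals the margin, and 8/1.18 = 6.8% equals the assumed SD.

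**4. Simulation, one BiV value.** There are three configurations with equal true mean gain of 18%. Their deviations are independent with SD 8/√2 = 5.66, so pairwise differences have SD 8. The Multivein value is multiplied by (1 + d). The documents give no d, so the range is assumed, as is the use of SD 8 for the Multivein contrasts.

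| Drift d | Multivein best, by value | Labels that differ from the percentage-change label |
|---|---|---|
| -10% | 1% | 32% |
| -5% | 10% | 23% |
| -2% | 22% | 11% |
| 0 | 33% | 0% |
| +2% | 46% | 13% |
| +5% | 64% | 31% |
| +10% | 87% | 53% |

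With percentage change from the adjacent baseline, a proportional drift cancels and the share is 33% throughout. With no mean drift but a between-patient drift SD of 5%, 20% of labels change.

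**5. Simulation, all seven settings.** Section 2 lists five BiV settings, of which posterior and anterior fall in the second part. Here BiV is the best of its five settings, and drift applies to posterior BiV, anterior BiV and Multivein.

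| Drift d | Multivein best, by value | Labels that differ |
|---|---|---|
| -5% | 3% | 16% |
| 0 | 14% | 0% |
| +5% | 27% | 19% |

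Taking the maximum over five settings gives BiV about 71% of labels under equal effects even without drift. Section 8.3 therefore also needs to say which BiV value is meant.

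**6. Cost of using the baseline.** The model of step 4 was rerun with no drift and an independent baseline error per setting. An assumed error of 1% changes about 10% of labels, and 2% changes about 19%. This noise does not favour or penalise Multivein; its share stays at 33%.

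**The case against.** **The scale may be loose wording.** Section 8.2 also speaks of a dP/dt max value for an endpoint that 8.1 defines as percentage change, and 6.2.2 speaks of the highest dP/dt max. A reader might infer that the plan has deliberately chosen the unadjusted value. The documents do not establish that. What stands is that the rule as written has no baseline term, and that the two readings can give different labels.

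**The drift is hypothetical.** This is true: no size appears in the documents. Atrial pacing at a constant rate removes one source of change, but it does not hold contractility constant over this time.

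**The parts are less rigid than Figure 4 suggests.** The legend to Figure 1 allows the catheter to move between lateral and posterior veins in either direction, and in the alternative second part it is not moved. The parts are still separated in time by the addition of a lead.

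**The one-value model overstates the effect.** This also stands. Drift reaches two of the five BiV settings, and with all seven settings the shift is smaller, though in the same direction.

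**Percentage change is not error-free.** Step 6 shows this. The differing labels in steps 4 and 5 are therefore changes from a drift-free label, not a count of errors in the study as it will be run.

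**Kappa need not fall.** Pressures are recorded time-aligned with LV pressure, so a shared drift could raise it.

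**Conclusion.** The concern holds, limited to the label used in the kappa analysis. Under equal true effects and assumed drifts of -5% and +5%, Multivein's share of best labels moves from 33% to 10% and 64% with one lateral BiV value, or from 14% to 3% and 27% with the best of five BiV settings. Between 16% and 31% of labels change. These figures rest on the assumed drift, on the plan's 18% and 8 points carried over to all configurations, and on independent deviations.

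Three stronger readings are not supported:

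- **That the primary result is compromised.** Standard BiV (lateral proximal) and Multispot are both in the first part, and Figure 4 lists them one after the other, so that contrast is largely unaffected.
- **That the sensors will look worse than they are.** Kappa can move either way.
- **That a reported proportion of patients with Multivein best will be biased.** The plan does not say that it will report one.

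This is one analysis for one of five secondary objectives in an exploratory study. It is worth correcting because the better rule is already used in 8.1 and the data for it are already collected.

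**What to change.** In section 8.3:

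- Define the best configuration as the one with the largest mean percentage change in dP/dt max from the adjacent AAI runs, averaged over repetitions.
- State which BiV value enters the label, for example the reference RV-LV lateral proximal setting.
- Derive labels for pressure-type sensors as change from the same AAI runs. Leave sensors with no AAI counterpart, such as the delay from RV pace to LV activation, on their own scale; AAI runs contain no RV pace.
- Keep the label based on the unadjusted value as a sensitivity analysis.

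The cost is a few sentences and no new data. Section 8.3 allows a change of analysis method without an amendment if no objective changes, with the justification given in the study report. It should be settled before the data are analysed, so that the choice between two rules is not made after seeing the results. The downside is the baseline noise of step 6 (about 10% of labels at an assumed 1% error per setting), which averaging four runs of about 20 beats should limit.
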